#### Quantitative research approaches–study population

All statutory insured persons of the above mentioned statutory insurance company (AOK Lower Saxony) that were diagnosed with relapsing or progressing MS (ICD.-10 G35.-) in 2019 or 2020 are included in the quantitative study. To define the study population, the following further refinement of the criteria for a MS diagnosis applies: (a) at least two diagnoses in two different quarters in the outpatient setting (M2Q-criterion); (b) at least one outpatient diagnosis with additional course-modifying MS therapy; or (c) at least one outpatient diagnosis with at least one diagnosis in the inpatient setting (as the principal or secondary diagnosis). Diagnosed PwMS are eligible if they are at least 18 years of age and live in the federal state of Lower Saxony. All eligible PwMS (n~7,000) will be included in the secondary data analysis of the statutory insurance data. Amongst those, all are invited to take part in the online survey by written letters. Additionally, for those taking part in the online survey (anticipated response: 25%: n~1,750), the survey data will be linked with the secondary data from the statutory insurance company and MS registry.

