#### Quantitative research approaches–sample size calculation for the online survey

The sample size calculation is based on the study’s primary endpoint, as defined by the PACIC–Short Form [23, 24]. Since there is limited information on MS healthcare and as this study is limited to the federal state of Lower Saxony, there is insufficient information on effect sizes in the literature. Therefore, the sample size calculation aims at being able to detect even small effects [60]. In order to avoid an alpha-error accumulation by multiple testing (four tests), the following Bonferroni correction [61] of the significance level is applied in the analysis: alpha_adj_ = alpha/N_tests_ = 0.05/4 = 0.0125. For a test design with a power of 90% (1—beta = 0.9) and a significance level of 1.25% (alpha_adj_ = 0.0125), a case number of 1,432 subjects is required for the significant detection of a small difference (effect strength d = 0.2) [62]. Considering a dropout of 75%, this results in a sample size of 5,728 (required case number of 1,432 subjects + expected dropout of 4,296 subjects = 5,728 subjects). The sample size of approximately 7,000, which compromises the entire population of insured PwMS by AOK Lower Saxony who fulfil the inclusion criteria, will be sufficient for evaluations according to various strata (e.g. age, sex, place of residence).

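### The claim that about 7,000 is sufficient for stratified evaluations is not supported for the survey endpoint, which only about 1,750 responders will have

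*Protocol article*

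**What the plan says.** All of the following is in the protocol article.

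- **Basis of the calculation** (sample size calculation for the online survey): "The sample size calculation is based on the study’s primary endpoint, as defined by the PACIC–Short Form". The section on the primary data of the online survey places this instrument in the questionnaire, so only responders have a score.
- **Inputs** (same section): the significance level is "alpha/N_tests_ = 0.05/4 = 0.0125", power is 90%, and the target is the "significant detection of a small difference (effect strength d = 0.2").
- **Result** (same section): "a case number of 1,432 subjects is required", and then "Considering a dropout of 75%, this results in a sample size of 5,728".
- **Sufficiency sentence** (same section): the roughly 7,000 eligible insured persons "will be sufficient for evaluations according to various strata (e.g. age, sex, place of residence"). No number of strata, stratum size, type of comparison or power accompanies it.
- **Expected responders** (study population of the quantitative part): everyone eligible is invited, and linkage is planned "for those taking part in the online survey (anticipated response: 25%: n~1,750"). Table 1 gives the same 7,000 and 1,750.
- **Planned comparisons** (primary data of the online survey): the primary endpoint is to be compared by region (three types), sex, severity and course of MS.

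**The concern.** The sentence ends a calculation for a survey endpoint, yet the number it calls sufficient is the number of invitations. After the 25% response that the plan itself expects, the reserve over the requirement for a single two-group comparison is small. Nothing in the section shows that this reserve covers strata.

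It matters because regional and subgroup differences are central to the project. The data analysis section assigns confirmatory methods to regional differences in utilisation and health outcomes, and the study is meant to lead to recommendations by type of region. A reader who has been told that the strata are large enough could take a non-significant result in a small stratum, or between unequal strata, as evidence that care does not differ.

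**Working it through.** **Inputs from the document:** d = 0.2; alpha 0.0125; power 90%; non-response 75%; 7,000 invited; 25% response.

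**Inferred:** a two-sided test of two equal groups. The document states neither, but this reproduces its figure; a one-sided test gives 1,242.

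**Assumed:** all stratum sizes, since the document gives none.

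**1. The plan's own figures.** The normal quantiles are 2.498 (two-sided 0.0125) and 1.282 (90% power), sum 3.779 before rounding.
- n per group = 2 × (3.779/0.2)² = 714.1, so 715, or 1,430 in total. The noncentral t distribution gives 716 per group, or 1,432, with power 0.900. The stated figure is reproduced.
- 1,432/(1 − 0.75) = 5,728. Reproduced.

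**2. Expected survey sample.**
- 7,000 × 0.25 = 1,750.
- 1,750 − 1,432 = 318.
- 1,432/1,750 = 82%: a stratum must hold this share of all responders to keep 90% power for a comparison inside it.

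**3. Formulas.** For groups of n₁ and n₂:
- power = Φ(0.2 × √(n₁n₂/(n₁+n₂)) − 2.498)
- d detectable with 90% power = 3.779/√(n₁n₂/(n₁+n₂))

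The noncentral t distribution agrees to within about 0.3 percentage points.

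**4. Reading A: two equal groups compared inside one stratum.** Here n₁n₂/(n₁+n₂) = n/4 for a stratum of n responders.

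| Stratum | Responders | Power at d = 0.2 | Detectable d (90% power) |
|---|---|---|---|
| One half | 875 | 68% | 0.26 |
| One third | 583 | 47% | 0.31 |
| One fifth | 350 | 27% | 0.40 |

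In any split into two or more strata the smallest holds at most 875 responders, so 68% is its ceiling. At an unadjusted alpha of 0.05, halves give 84% and thirds about 68%.

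**5. Reading B: strata compared with each other across all responders.**

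| Comparison | n₁n₂/(n₁+n₂) | Power at d = 0.2 | Detectable d (90% power) |
|---|---|---|---|
| 50:50 (875 v 875) | 437.5 | 95% | 0.18 |
| 70:30 (1,225 v 525) | 367.5 | 91% | 0.20 |
| Two of three equal regions (583 v 583) | 291.7 | 82% | 0.22 |
| 80:20 (1,400 v 350) | 280 | 80% | 0.23 |
| 90:10 (1,575 v 175) | 157.5 | about 50% | 0.30 |

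- **Limit for 90% power:** 1,750 × p(1 − p) ≥ (3.779/0.2)² = 357, so p(1 − p) ≥ 0.204, which gives p up to about 0.71.
- **Regions:** three equal regions with 716 responders each need 3 × 716 = 2,148 responders, or 2,148/0.25 = 8,592 invited, more than the 7,000 available.
- **Relevance of 90:10:** the Introduction puts primary progression at about 10% of people with MS. Whether responders would show that share, or be compared in that way, is an assumption.

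**6. Contrast.** If all 7,000 had a score, comparisons inside two, three or four equal strata would have over 99.9%, 99% and 95% power. For comparisons inside strata, the sentence is true of the invited number and not of the expected responders.

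**The case against.** **The sentence may mean only that strata are compared with each other.** This is plausible. The four factors named for the primary endpoint match the four Bonferroni tests, and no comparison nested inside a stratum is specified. On this reading the survey does well for balanced groups (95%) and moderately unequal ones (91% at 70:30). It still falls short for pairs of regions and for splits beyond about 71:29, so an unqualified claim of sufficiency does not follow.

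**7,000 is set beside 5,728, and both are numbers before non-response.** Correct. That comparison is consistent, and the 1,750 is stated openly elsewhere. A reader might infer an arithmetic error, but there is none. What lacks support is the further step to strata.

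**All 7,000 are available in the insurance data.** Also correct, and the sentence is tenable there. But it stands in the survey section, and those data contain no PACIC score.

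**The plan sets no 90% target within strata.** This stands. A reader might infer that a stated target is missed, but the 90% belongs to the overall test. The within-stratum figures show what the plan's inputs imply, not a broken commitment.

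**Some strata could reach 1,432.** This stands too. A stratum with at least 82% of responders would, and the document gives no split by age, sex or residence. It can only be said that the smallest stratum of a split cannot.

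**Conclusion.** The sufficiency statement is unsupported as written for the survey's primary endpoint. Inside strata, the smallest has at most 68% power to detect d = 0.2. Between strata, 90% power holds only up to about 71:29, with 82% for a pair of three equal regions and about 50% at 90:10. These figures rest on the 25% response being met, a two-sided alpha of 0.0125 and assumed stratum sizes.

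One opposite inference should also be avoided: because 1,750 exceeds 1,432, a reader might conclude that the survey is large enough for all the planned overall comparisons. The 1,432 applies to two equal groups. Region has three levels, and the split by sex, severity or course is not given.

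Severity is moderate. The base calculation is correct, no test or endpoint changes, and the survey already invites everyone eligible, so the remedy is an accurate statement and not a larger sample.

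**What to change.** 1. Restrict the sufficiency statement for 7,000 to the insurance-data analyses.
2. For the survey, state that about 1,750 expected responders give at least 90% power for d = 0.2 only in two-group comparisons no more unequal than about 71:29.
3. Give the lower power or the detectable d for the three-region comparison and for the unequal comparisons, using the expected group sizes.
4. Say which strata are meant, and whether they are compared with each other or analysed separately.
5. Report within-stratum survey results as estimates with confidence intervals, and do not read a null result as no difference.
6. Do not replace the sentence with a claim that 1,750 suffices for all overall comparisons.

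The cost is wording and a short table. The drawback is that a stated property of the study becomes less favourable.

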#### Quantitative research approaches–data analysis

The resulting health outcomes that will be evaluated by descriptive analyses are for example patient-relevant outcomes, such as HRQoL, the number of relapses per year and satisfaction with MS healthcare. Correlational analyses will be used to examine associations with parameters, such as healthcare service utilisation and costs (and others). Regional differences in healthcare service utilisation and the resulting health outcomes will be analysed using confirmatory statistical methods (such as inferential statistical tests) and multivariate regression models.

Based on the guideline recommendations [8, 9] and the subjective needs of PwMS (drawn from the online survey), model estimates will be calculated to determine the need for healthcare provisions and the associated costs of needs-based healthcare in Lower Saxony. The total number of PwMS; the distribution of forms and severity; and the average number of relapses will be included in the model.

Finally, whether the supply of care in Lower Saxony meets the needs of PwMS will be analysed by comparing the existing resources and requirements. Analyses will be carried out using the software programs SAS, R and SPSS and Microsoft Excel.

#### Ethical considerations and data management

This study was approved by the Ethics Committee of the Hannover Medical School on 24 June 2020 (reference number 9173_BO_K_2020) and by the University of Oldenburg on 06 August 2020 (reference number 2020–108). Whenever necessary, approval of changes of the initial study protocol was and will be obtained from the ethics committees of Hannover Medical School and/or University of Oldenburg. The study is and will be conducted in accordance with the principles of the Declaration of Helsinki. The principles of ‘Good Clinical Practice’ and all relevant legal, ethical and data protection principles will be adhered to. All persons actively participating in the study will be fully and comprehensibly informed about the project’s purpose and procedure and the handling of the collected data. Whenever necessary, the research team obtains informed consent for the qualitative (written consent) and quantitative (online consent) research approaches regarding the legal, ethical and data protection principles. Participation in the study is voluntary and can be withdrawn at any time. Data already collected will then be deleted. Non-participation has no consequences. Data will be deleted ten years after the end of the project.

Details regarding the qualitative research approaches: The participants of the focus groups and the future workshop will be informed that their participation is voluntary and that they have a right to refuse or withdraw from the study without any consequences. The audio-recorded data will be transcribed and analysed without personal information and deleted after the transcription is complete. Access to data is limited to selected members of the project team.

Details regarding the online survey: The statutory health insurance company invites insured persons who fulfil the inclusion criteria. The MS registry, which is another project partner, hosts the online survey and informs the statutory health insurance company using pseudonyms to ensure the confidentiality of the collected data and allow non-responder analyses. The statutory health insurance company will not receive any information from the completed questionnaire, and the MS registry will not obtain any of the participants’ personal information, apart from the answers provided in the online survey. The Hannover Medical School receives pseudonymised data from the statutory health insurance company, the online survey and the MS registry for linkage and evaluation. Linkage is possible using pseudonyms and a matching table that were previously generated by an independent trust agency. However, project partners that evaluate the linked data will not receive any information that could result in the participants being identified. In accordance with § 75 of the German Social Code, Book X (SGB X), the transfer of the claims data for the research purpose will be legitimated by the competent supervisory authority (Ministry for Social Affairs of Lower Saxony; German: Niedersächsisches Ministerium für Soziales, Gesundheit und Gleichstellung). Access to data is limited to selected members of the project team.

#### Derivation of recommendations for action

Considering the results of the literature searches, focus groups, online survey, secondary data and future workshop, recommendations for action to improve the healthcare for PwMS will be developed within a workshop, which will involve all project partners and experts who are advising the entire project.

The project aims to generate reliable statements regarding the needs for care; current care structures and processes; utilisation of healthcare services; and resulting health outcomes. The results of the study will contribute to the identification of the differences between rural, urban and metropolitan regions and deficits in care. The analyses, alongside the statutory health insurance data and information from those involved in treatment structures, allow the optimisation of healthcare for PwMS, including pharmaceutical therapy, other therapeutic measures (e.g. physiotherapy, speech and occupational therapy) and assistive devices. In rural, urban and metropolitan regions, the infrastructure can be optimised in a patient-oriented manner for all areas of life affected by MS. The results and models can form the basis to pilot and evaluate a new form of healthcare.

## Discussion

To the best of our knowledge, this is the first study to consider and link various data sources (linkage of quantitative data: secondary data of statutory insurance and MS registry data with primary data from the online survey; and qualitative data sources: focus groups and future workshop) to determine the current healthcare provision of PwMS in Germany and how it is perceived by those affected based on a large patient population. The strength of the project is derived from the analyses of different data sources and perspectives from various research approaches. The patients’ perspective is complemented by the perspective of professionals in the context of healthcare for PwMS and the secondary data from the statutory health insurance company and MS registry. This enables precise recommendations regarding the optimisation of healthcare for PwMS, including pharmaceutical therapy, other non-physician therapies (physiotherapy, speech and occupational therapy) and assistive devices. The results and model suggestions can form the basis to pilot and evaluate a new form of healthcare. As Lower Saxony contains a mixture of rural, urban and metropolitan regions, we expect that our results can be used as a template for similar regions in Germany to optimise the healthcare for PwMS outside of the studied region.

The main methodological challenges in this project relate to the representativeness of the of the recruited study population. The qualitative approaches do not aim to generate representative findings; instead, they aim to identify thematic areas for further investigation. Therefore, the goal of the online survey is to obtain reliable statements from the patients’ perspective regarding healthcare for PwMS in Lower Saxony. A possible selection bias must be investigated. Focusing on this aspect, one study published in 2013 [63] showed no significant differences in the age and sex distribution between those insured by AOK Lower Saxony and the general population of Germany. However, on average, although those insured by AOK Lower Saxony differ in terms of occupation from the general population, in the group of PwMS, higher occupational groups should be sufficiently represented to enable accurate analyses. Additionally, a non-responder analysis will be conducted and, if necessary, further computational adjustments will be made to the data set. Therefore, the basic information (e.g. age and sex) of those taking part and not taking part in the survey will be compared. Moreover, whether there is a significant difference between those groups will be checked using a t-test or Chi^2^-test.

To proactively minimise a possible participation bias, the study is promoted using various platforms of the DMSG Lower Saxony and AOK Lower Saxony. The invitation letters for the online survey are developed in close coordination with the DMSG Lower Saxony, and postal reminders are sent out after two and four weeks. Furthermore, a telephone contact will be offered.

Study results will be disseminated via national and international conference presentations and publications in peer-reviewed journals. Project partners will additionally publish results of the project in non-scientific language on their homepages and member journals.

MS is a lifelong disease that manifests at a young age in various clinical appearances [4]. Therefore, personalised care according to the individual needs of PwMS is essential to positively influence the progression of MS and ensure a lasting participation in PwMS’s social lives and work. As the progression of the disease can be positively and negatively influenced by factors that may interact, the use of preventive measures is indicated. The identification of barriers in the healthcare sector based on the knowledge gained in this study allows conclusions to be drawn regarding the optimisation of structures and processes in the overall treatment for MS.

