#### Focus 1: Data used to analyse general healthcare for PwMS–secondary data from a statutory health insurance company

Secondary data from a statutory health insurance company is collected for billing purposes and includes information on socio-demography, comorbidities, longitudinal utilisation of services and cost data for various aspects of healthcare for PwMS (e.g. outpatient and inpatient diagnoses, prescribed pharmaceuticals or sick leave). With this data source, the differences in healthcare utilisation between various patient groups can be identified.

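### Non-response adjustment is conditional, and the only check stated is a significance test on basic data such as age and sex; default weighting on the claims data of all invitees would serve better

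*Protocol article*

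**What the plan says.** The Discussion of the protocol article treats representativeness as the main methodological challenge. Its answer for the survey is: "Additionally, a non-responder analysis will be conducted and, if necessary, further computational adjustments will be made to the data set". It goes on that "the basic information (e.g. age and sex) of those taking part and not taking part in the survey will be compared", and that "whether there is a significant difference between those groups will be checked using a t-test" or a chi-square test. It gives no other criterion for when adjustment is needed, no significance level and no adjustment method.

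Other sections describe what is available for this purpose:

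- The section on the quantitative study population says: "All eligible PwMS (n~7,000) will be included in the secondary data analysis of the statutory insurance data". It continues: "Amongst those, all are invited to take part in the online survey by written letters". The response figure there is "anticipated response: 25%: n~1,750".
- The sample size section uses the same rate: "Considering a dropout of 75%, this results in a sample size of 5,728".
- The section on the insurer's secondary data says that this source "includes information on socio-demography, comorbidities, longitudinal utilisation of services and cost data".
- *Ethical considerations and data management* states that the registry, which hosts the survey, reports to the insurer by pseudonym, partly so that non-responders can be analysed.

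Nothing in the article says that the richer claims variables will be used to compare responders with non-responders or to weight the survey.

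**The concern.** A significance test is a poor guide to whether non-response needs correction, for two reasons.

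1. Its result depends on the number of people as much as on the size of the imbalance. At this size it reacts to differences that hardly matter.
2. It speaks only about the variables tested. Comorbidity, treatment and use of care may plausibly influence both who completes an online questionnaire and how people rate their care. If selection runs through these, age and sex can look balanced while the survey results are shifted.

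The stake is the level of the patient-reported results. The study's primary objective is patient-rated quality of care. The data-analysis section also reports HRQoL and satisfaction descriptively, and carries survey-based needs into estimates of required care and its cost for Lower Saxony. A shift in level passes into all of these. The study already holds claims data on the people who do not answer.

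**Working it through.** **The plan's own figures.** For d = 0.2, alpha = 0.05/4 = 0.0125 and 90% power, the two-sided normal formula gives 715 per group, or 1,430 in total. The t-based solution is 1,431.4, which rounds up to the stated 1,432. (The article does not state sidedness; one-sided gives 1,242 and does not match.) Allowing for 75% non-response, 1,432 / 0.25 = 5,728, as stated. There is no arithmetic error, and this point does not rest on one.

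**Inputs.** From the article: about 7,000 invitees and 25% response, so 0.25 × 7,000 = 1,750 responders and 5,250 non-responders. Assumed, because the article gives none: a 5% two-sided level for the check, and the size of selection.

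**Step 1: what the test reacts to.**
- SE of a standardised difference = sqrt(1/1,750 + 1/5,250) = 0.0276.
- Smallest significant difference = 1.96 × 0.0276 = 0.054.
- Power is 80% at 0.077 and about 95% at 0.10.
- With an assumed age SD of 12 years, 0.054 is 0.054 × 12 = 0.65 years. With an assumed 70% women, it is 0.054 × sqrt(0.7 × 0.3) = 0.025, or 2.5 percentage points.

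The test is therefore very sensitive to imbalance in what it tests.

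**Step 2: what non-response does to a mean.**
- Bias of the responder mean = (1 − response) × (responder mean − non-responder mean) = 0.75 × delta.
- SE of a mean on 1,750 = 1/sqrt(1,750) = 0.0239 SD.

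| Assumed delta (SD) | Bias (SD) | Bias in standard errors |
|---|---|---|
| 0.1 | 0.075 | 3.1 |
| 0.2 | 0.150 | 6.3 |
| 0.3 | 0.225 | 9.4 |

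**Step 3: what non-response does to a contrast.** In each group the bias is (1 − that group's response) × that group's delta. The contrast carries the difference of the two. With 25% response and delta = 0.2 in both groups, this is 0.150 − 0.150 = 0. It is non-zero only if response or delta differs between the groups.

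**Step 4: can the age/sex check miss the bias?** An illustrative simulation had 300 runs, with every parameter assumed. There were 7,000 people and about 25% responded. Response depended on a severity variable of the kind claims might capture (log-odds 0.4 per SD). That variable was independent of age and sex and correlated 0.3 with the outcome.
- The age or sex test was significant in about 10% of runs, which is the false-positive rate of two 5% tests (1 − 0.95² = 0.0975).
- Bias of the responder mean was 0.087 SD unweighted, 0.087 SD after weighting on age and sex, and about 0.000 SD once severity entered the weights.

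The simulation is built so that age and sex carry nothing. It shows that the check can miss bias, not how large the bias will be in this study.

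**The case against.** Several objections have force.

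- **A formal trigger is not written down.** A reader might infer that adjustment happens only if p < 0.05. That is the natural reading of a conditional adjustment followed directly by significance tests, but the article states no such rule and no level.
- **The variable list is open.** Age and sex are examples, and a full protocol or analysis plan, not shown here, may name more variables and the adjustment method. Those details are not faulted here. The article does, however, commit itself to significance testing of basic information, and that choice can be judged.
- **A reader might conclude that the check cannot detect or remove bias at all.** That goes too far. Step 1 shows high sensitivity for the variables tested, and adjusting for them removes the share of bias they explain. Over-sensitivity also makes adjustment more likely, not less. The harm comes from variables that are not tested.
- **It is tempting to set 0.075 to 0.225 SD against d = 0.2 and call the powered comparisons compromised.** The first is bias in an overall mean and the second is a difference between groups. Selection that shifts both groups equally cancels, and the article gives no evidence that selection differs between them.
- **Claims weighting has limits.** Disability is measured in the survey (PDDS) and is not in the article's description of the claims, so weights reach it only by proxy. They do not reach selection on satisfaction itself.
- **The data flow is not fully described.** Linkage to survey data is set out only for participants. The insurer learns who responded, but the article does not say that the analysing team receives this indicator on every claims record.
- **The risk is acknowledged.** The article plans promotion, two postal reminders and telephone contact. These may reduce non-response but do not replace adjustment.

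What remains is that the one stated check is weak for its purpose and a better one is within reach.

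**Conclusion.** The point holds in a limited form. A non-significant result on basic variables would not show that the survey is free of selection bias, because it covers only what those variables carry. If selection runs through untested characteristics, following the stated approach could leave overall levels shifted by 0.075 to 0.225 SD. That range assumes a responder/non-responder difference of 0.1 to 0.3 SD and the 25% response the article expects. The article gives no estimate of the actual difference, so it is not established that selection is the dominant error.

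The exposure lies mainly in the PACIC mean, HRQoL, satisfaction, and the needs and cost estimates. Bias in the PACIC contrasts by region, sex, severity and course has not been shown.

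This is a cheap improvement to the analysis, not a must-fix.

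**What to change.** - Replace the t-test and chi-square check with standardised differences between responders and non-responders.
- Fit a response model in all 7,000 or so invitees on pre-specified claims variables, for example age, sex, region, coded MS course, comorbidity, disease-modifying therapy, utilisation and costs.
- By default, use the resulting response weights (or calibration to the same variables) in the PACIC, HRQoL, satisfaction and needs analyses, whatever any test shows. Present unweighted results alongside.
- Add a sensitivity analysis for selection that the claims do not explain, such as a range of assumed responder/non-responder differences put through the 0.75 × delta relation.

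Cost: revised analysis wording, modest programming and somewhat wider intervals from weighting. The team must also confirm that the insurer can supply the listed variables with a pseudonymised responder indicator on all claims records. The sample size does not change.
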